### Objectives

The primary objective 1 of PP1 is to systematically characterize patients consecutively admitted to a psychiatric inpatient unit with any current form of clinically diagnosed depressive episode that is part of MDD, and not of bipolar disorder.

The primary objective 2 of PP2 is to evaluate the validity of the clinical diagnosis of moderate or severe unipolar depressive in inpatients using a gold-standard research interview, and the predictors of the diagnostic concordance/discordance.

The primary objective 3 of PP3 is to conduct a 6-month, prospective, naturalistic follow-up study in a subgroup of PP2 that has verified moderate to severe MDD and ongoing suicidality using structured assessments of the duration and severity of suicidality, the frequency of recurrence of suicidality as well as any significant moderators and mediators.

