Hypothesis 3A: We hypothesize that the time to remission of suicidal symptoms after the baseline is a major determinant of shorter overall duration of passive or active suicidal ideation (PASI) during the entire 6-month observation period.

Hypothesis 3B: We hypothesize that the rate of remission of suicidal symptoms after baseline is a major determinant of lower recurrence of PASI during the 6-month observation period.

Hypothesis 3C and 3D: We hypothesize that a longer total duration of PASI (Hypothesis 3C) and a greater risk of recurrence of PASI after complete remission (Hypothesis 3D) during the 6-month observational phase is associated with the following factors at time T0 (i.e., “moderators”): greater severity of (i) depressive symptoms [28, 36, 42, 43], (ii) manic symptoms (below the threshold of (hypo)mania as part of MDD), (iii) anxiety symptoms [28, 36, 45], (iv) anger and hostility [43], (v) quality of life impairment [48, 49], (vi) global symptoms of illness and (vii) suicidality [28, 36, 42, 47], (viii) higher number of lifetime depressive episodes, (viii) index admission as part of a psychiatric emergency, (ix) longer duration of current depressive episode [44], (x) higher non-adherence to pharmacological and non-pharmacological treatments, (xi) comorbid borderline personality disorder [35, 46], and (xii) comorbid substance use diagnosis [28].

Exploratory study aim 1 of PP3 is to describe the association between PASI and suicide attempts (S-STS item 14) as well as with the utilization of outpatient and inpatient care services during the 6-month observation period.

Exploratory hypothesis 1A, 1B and 1C: We hypothesize that a higher number of days with PASI (exploratory hypothesis 1A), a higher number of days with active suicidal ideation (exploratory hypothesis 1B) and a higher number of suicide attempts (exploratory hypothesis 1C) during the 6-month observation period are significantly associated with a higher number of (i) outpatient appointments, (ii) emergency department visits, (iii) inpatient hospitalizations, (iv) hospitalizations as part of psychiatric emergencies, (v) psychiatric hospital bed days, and (vi) suicide-related hospital bed days.

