Hypotheses 3A and 3C will be analyzed by means of methods for count data, such as Poisson or Negative Binomial models, depending on whether overdispersion is present in the data or not. The dependent variable will be overall duration of PASI during the 6-month observation period and the independent variable of main interest will be time to remission of suicidal symptoms after baseline.

Hypotheses 3B and 3D will be analyzed by using Cox proportional hazard models, where the dependent variable will be time-to-first-recurrence of PASI and the independent variable of main interest will be time to remission of suicidal symptoms after baseline.

Further independent variables for regression analysis will include patient, illness, and treatment variables, including severity of depressive symptoms (MADRS, Quality of Life in Depression Scale (QIDS-S) [79]), manic symptoms (YMRS), anxiety (BAI), anger/hostility (STAXI, AF-BP), global illness symptoms (CGI-S), quality of life (EQ-5-DL), and suicidality (S-STS); presence of psychiatric emergencies; number of lifetime depressive episodes; duration of current depressive episode; nonadherence to pharmacological and nonpharmacological treatments; and comorbid borderline personality and substance abuse. Additionally, a random factor accounting for clustering of patients in centers will be added to the models.

Assuming a minimum requirement of 10 patients per predictor variable in regression analyses [91–93] and approximately 20 independent patient, illness, and treatment variables that would be tested as potential correlates of time to remission of suicidality, we estimated that a sample size of at least 200 would be required.

Additionally, as a secondary analysis, we will divide patients into two groups using the median time up to the first S-STS value of zero, which are either below or above the median time to first complete remission of suicidality.

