Furthermore, comparisons between the slower and faster remitting group of continuous variables will be performed using multiple comparison procedures (MCPs) with 3 measurement time points (T1, T2, and T4). Because only the primary outcome and very limited other parameters are collected by telephone at T3, data at T3 are not included in these analyses. Because the timing at T2 (hospital discharge) is variable, and this timing is not independent of the outcome measured, the duration between T1 and T2 is included as a covariate in the analyses. Cross-group comparisons of dichotomized or categorical variables are performed using chi-square statistics. For ease of comparison, continuous outcomes, such as depressive symptoms and medication use are calculated. All analyses are two-sided, with alpha = 0.05. Due to the exploratory nature of the study, no adjustment for multiplicity between different endpoints is conducted. Hence, p-values and confidence intervals need to be interpreted in a hypothesis-generating manner. In addition, multivariable regression analysis with backward selection will be performed to identify independent moderators or mediators of continuous and categorical outcomes, respectively. Moreover, missing continuous data will be treated using multiple imputation using chained equations and random effects for the clustering of patients in different centers.

Among the exploratory objectives, the patient, illness, and treatment factors that influence the risk of different levels of active suicidality are identified: i) active suicidality (S-STS item 3), ii) active suicidality with preparatory action (S-STS item 12), iii) self-injurious behavior without suicidal intent (S-STS item 13), and iv) suicide attempt (S-STS item 14) during the observation period of inpatient treatment and within 6 months of study inclusion (T1). Target parameters i)-iv) are associated with slower initial resolution of suicidality (lower than median time to S-STS score = 0); and with: Depressive symptom severity (MADRS, QIDS-S), manic symptoms (YMRS), anxiety (BAI), anger/hostility (STAXI, AF-BP), and global illness symptoms (CGI-S); higher number of lifetime depressive episodes; more frequent psychiatric emergencies; longer duration of current depressive episode; non-adherence to pharmacological and non-pharmacological treatments; comorbid borderline personality; and substance abuse diagnoses.

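### Primary objective 3 promises moderators and mediators, but the stated regression with backward selection can support only claims about predictors

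*Protocol article*

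**What the plan says.** All places are in the Protocol article.

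- **Objectives.** Primary objective 3, for the follow-up population (PP3), covers duration and severity of suicidality and "the frequency of recurrence of suicidality as well as any significant moderators and mediators".
- **Aims and hypotheses, Hypotheses 3C and 3D.** Longer total duration of suicidal ideation, and greater risk of its recurrence, "is associated with the following factors at time T0 (i.e., “moderators". The word stands in quotation marks and is explained as a T0 factor associated with the outcome.
- **Sample size and statistical analyses, models for 3A to 3D.** In both the count models and the Cox models, "the independent variable of main interest will be time to remission of suicidal symptoms after baseline". The other factors join it in the same role: "Further independent variables for regression analysis will include patient, illness, and treatment variables".
- **Same section, sample size.** The size rests on a rule of thumb, "Assuming a minimum requirement of 10 patients per predictor variable in regression analyses", applied to "approximately 20 independent patient, illness, and treatment variables that would be tested as potential correlates of time to remission of suicidality".
- **Same section, selection step.** "multivariable regression analysis with backward selection will be performed to identify independent moderators or mediators of continuous and categorical outcomes".

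The article names no interaction term, no relationship to be moderated, no candidate mediator and no indirect effect.

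**The concern.** Three different null hypotheses sit behind three different words.

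- *Predictor*: the factor has no association with the outcome, given the other variables.
- *Moderator*, in its usual sense: the effect of some named exposure on the outcome does not vary with the factor. This needs an interaction.
- *Mediator*: no part of the exposure's effect runs through the variable. This needs a path from exposure to mediator and one from mediator to outcome, with the mediator measured between the two.

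Backward selection over single-term variables tests only the first. The objective and the selection step claim the second and third. A purely prognostic factor would therefore be reported as a moderator or mediator. A factor that modifies another relationship but has little or no main effect would usually be dropped. The Background says the results may direct clinicians to subgroups at risk and possibly help to devise a standard of care. Prediction serves the first of these uses. A result labelled *moderator* or *mediator* invites a reading as effect modification or mechanism, which the analysis has not examined.

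**Working it through.** **1. The plan's own size.** Inputs from Sample size and statistical analyses: 10 patients per predictor, about 20 predictors, 315 enrolled, 34% attrition.

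- Required: 10 × 20 = 200.
- Expected at month 6: 315 × (1 − 0.34) = 207.9, stated as 208. The earlier assumption gives the same: 260 × 0.80 = 208.

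Both figures reproduce. The requirement of 200 covers single-term predictors only. The margin is 208 − 200 = 8 patients, less than the 10 needed for one more term.

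**2. Room for interactions under that rule.** Suppose time to remission is one of the 20 variables and each of the other 19 gets an interaction with it.

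- Terms: 20 + 19 = 39.
- Completers required: 10 × 39 = 390.
- Enrolment required: 390 / 0.66 = 590.9, so 591.
- Patients per term at the planned size: 208 / 39 = 5.3.

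If time to remission comes on top of the 20, there are 1 + 20 + 20 = 41 terms. That needs 410 completers and 410 / 0.66 = 621.2, so 622 enrolled. On either count a full set of interactions is out of reach. Even a few would have to displace some single-term candidates if the rule is to be kept.

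**3. What the selection step responds to.** This is an illustration by simulation. Assumptions, none from the documents: n = 208, 20 independent standard normal covariates, linear outcome with residual SD 1, slopes of 0.3, backward elimination at two-sided 0.05, 2,000 runs. Time to remission stands in as the exposure, which is a choice made here.

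| Factor | Kept by backward selection | Flagged by interaction test |
|---|---|---|
| Prognostic, no interaction | 98.5% | 6.6% |
| Modifies the exposure effect, no main effect | 7.5% | 97.4% |
| Noise variables (average) | 5.2% | not run |

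The 6.6% and 7.5% lie a little above 5% because the fitted model in each case omits the true interaction.

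**4. Sensitivity to the assumed effect.** One factor, no selection, n = 208, 2,000 runs:

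| Case | Main-effect test | Test of the matching claim |
|---|---|---|
| Prognostic only, 0.25 SD | 95% | interaction 5% |
| Modifier only, 0.25 SD | 6% | interaction 93% |
| Prognostic only, 0.15 SD | 57% | interaction 5% |
| Modifier only, 0.15 SD | 4% | interaction 59% |
| Predicts outcome, unrelated to exposure (no mediation), 0.25 SD | 95% | both paths jointly 5% to 6% |

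The rates move with the effect size, but the pattern does not, because each test answers its own null hypothesis.

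**The case against.** **The document defines its term.** Hypotheses 3C and 3D gloss *moderators* as T0 factors associated with the outcome. This stands. A reader might infer that the regressions are the wrong analysis for 3C and 3D, and the text does not support that. They are association hypotheses, and regression tests them properly. The gloss does not reach *mediators*, which is never defined. Nor is it repeated in the objective or the selection step, where both words stand without qualification.

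**The moderated relationship is not the plan's.** Nothing says that factors modify the effect of time to remission. This stands too. A reader might infer that the plan will miss true moderators in general. That holds only for a factor with little or no main effect. One that also has a main effect would tend to be retained, though not shown to moderate anything.

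**The simulation is close to definitional.** It sets one term to zero and shows that each test finds its own target. It is also linear, with assumed effects, where the plan uses count and Cox models. This is fair. The figures illustrate the mismatch and do not forecast error rates for this study.

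**Candidates are not all baseline factors.** Treatment variables, adherence and psychiatric emergencies are recorded at later visits, so it cannot be said that no candidate could be a mediator. This stands, but selection in a regression still would not show that one is.

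**An analysis plan may add the missing terms.** It may, and single-term entry is an inference from the hypotheses and the predictor count. But the article already fixes both the tool and the claim, so an analysis plan that follows it inherits the mismatch.

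**Results are hypothesis-generating.** That sentence follows from the lack of multiplicity adjustment. It tempers the strength of a finding but does not change which quantity was tested.

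**Conclusion.** The concern holds as a mismatch between the claim and the tool. As written, the plan supports statements that a factor predicts duration or recurrence of suicidality given the others. It does not support statements of effect modification, and it gives mediation neither a definition nor a method. The models themselves need not change for Hypotheses 3C and 3D.

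Its size is best stated by kind. A purely prognostic factor of moderate strength would nearly always be retained and could then carry either label (98.5% in the illustration). A factor that acts only by modifying another relationship would be retained little more often than noise (7.5% against 5.2%). These rates rest on assumed slopes of 0.3, independent covariates, a linear outcome and time to remission as the exposure. The structural point does not rest on them. It assumes only that candidates enter as single terms, as the hypotheses, the list of further variables and the count of about 20 predictors indicate.

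The matter deserves correction because the wording belongs to a primary objective and would shape the study's conclusions.

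**What to change.** 1. In Objectives, in Hypotheses 3C and 3D and in the selection step of Sample size and statistical analyses, replace *moderators and mediators* by *predictors (correlates)*. Add one sentence stating that no moderation or mediation conclusion will be drawn from these models.
2. If a moderation claim is kept, name the relationship being moderated and test a short list of interactions named in advance. Under the plan's 10-per-predictor rule, 208 completers cannot carry interactions for all variables, so say which single-term candidates give way or that the rule is relaxed.
3. If a mediation claim is kept, name the exposure, the mediator and the outcome, and estimate the indirect effect only through a variable measured after the exposure and before the outcome.

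Cost: the first step is wording only and needs no patients, data or new models. The others add a few pre-named analyses. The downside is fewer and weaker claims, since interactions are estimated less precisely than main effects.

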Exploratory study aim 2 of PP3 is to assess risk factors for different levels of active suicidality, consisting of active suicidal ideation (S-STS item 3), active suicidality with preparatory action (S-STS 12), self-injurious behavior without suicidal intent (S-STS item 13), or suicide attempts (S-STS item 14).

Exploratory study hypothesis 2: Active suicidality as defined above is associated with (i) slower rate of remission of suicidal symptoms after baseline, greater baseline severity of (ii) depressive symptoms, (iii) manic symptoms (below the threshold of (hypo)mania as part of MDD), (iv) anxiety symptoms, (v) anger and hostility, (vi) quality of life impairment (vii) global illness symptoms, and (viii) suicidality, (ix) higher number of lifetime depressive episodes, (x) duration of current depressive episode, (xi) index admission as part of psychiatric emergencies, (xii) higher non-adherence to pharmacological and non-pharmacological treatments, (xiii) comorbid borderline personality disorder, and (xiv) comorbid substance use diagnosis.

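### Exploratory aim 2 relates speed of remission to suicidal acts counted over the same six months, so slow remission can look like a risk factor without having come first

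*Protocol article*

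**What the plan says.** Under Aims and hypotheses, exploratory aim 2 sets out to "assess risk factors for different levels of active suicidality". The levels are active ideation (S-STS item 3), preparatory action (item 12), "self-injurious behavior without suicidal intent (S-STS item 13") and suicide attempt (item 14). The leading factor in the hypothesis is a "slower rate of remission of suicidal symptoms after baseline".

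Sample size and statistical analyses fixes both sides of this comparison. The outcomes end with "suicide attempt (S-STS item 14) during the observation period of inpatient treatment and within 6 months of study inclusion (T1"). The link between the two sides is stated as "Target parameters i)-iv) are associated with slower initial resolution of suicidality". The predictor is "slower initial resolution of suicidality (lower than median time to S-STS score = 0"). I read this as the half of patients with the longer times, although the parenthesis literally says lower. The same section explains how the halves are formed: "we will divide patients into two groups using the median time up to the first S-STS value of zero".

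After T1 the S-STS is given at discharge (T2), month 3 (T3) and month 6 (T4), according to Table 1. The Discussion describes these interviews as covering periods. Nothing limits the outcomes to acts after the first zero, sets a landmark, or treats remission as time-dependent.

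**The concern.** A risk factor has to be in place before the event it predicts. Here remission speed becomes known only as follow-up unfolds, over the same months in which the acts are counted. Three things follow:

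- An act before the first zero is an outcome. If its item enters the score and the act falls in the period the interview asks about (the look-back), it also postpones the zero. The predictor is then partly a consequence of the outcome.
- Slow remitters have more suicidal days before their first zero, and so more time in which an act can occur.
- A positive item 3 can hardly coexist with an S-STS value of zero. For active ideation, predictor and outcome are close to the same measurement.

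The Background says the results should point clinicians to subgroups at higher risk. Slow early remission could be reported as such a marker when the analysis has not shown that it came first.

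**Working it through.** **1. The plan's own figures.** 260 × 0.80 = 208 and 315 × 0.66 = 207.9, about 208 patients with month-6 data. 10 patients × 20 predictors = 200. These reproduce. No effect size or sample size is given for exploratory aim 2, so n = 208 is used below.

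**2. The two definitions side by side.**

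| | Predictor | Outcomes |
|---|---|---|
| Starts | T1 | T1 |
| Runs to | first S-STS zero, up to month 6 | month 6 |
| Instrument | S-STS value | S-STS items 3, 12, 13, 14 |
| Restricted in time? | no | no |

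**3. Acts independent of remission.** The document gives no act rates, remission times, discharge times or look-back, so all are assumed: 10%, 20% or 30% of patients with any act in six months, median remission 30 days, median discharge day 45, and an act inside the look-back preventing a zero. Patients are split at the median time to first zero and compared by two-sided chi-square at 0.05. Odds ratios come from 400,000 simulated patients and rejection rates from 1,500 trials of 208.

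| How the zero is found | Odds ratio, slow vs fast | Rejection rate (nominal 5%) |
|---|---|---|
| Daily, acts do not affect the score | 0.98–1.01 | 5.0–6.1% |
| Daily, 7-day look-back | 1.00 | 4.8–6.4% |
| Daily, 30-day look-back | 1.18 | 4.9–8.9% |
| T2/T3/T4, 7-day look-back | 1.09–1.10 | 5.9–6.9% |
| T2/T3/T4, 30-day look-back | 1.41–1.48 | 11–25% |
| T2/T3/T4, look-back to previous visit | 1.74–1.96 | 22–58% |

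Example from the last row, at 30% with an act: 36.9% of slow and 23.0% of fast remitters have one, so OR = (0.369 × 0.770)/(0.631 × 0.230) = 1.96.

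A second set of assumptions (5%, 10% or 20% with an attempt; median clearance 20, 35 or 60 days; median stay 35 days; zeros at visits only) gave:

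- 7-day look-back: 1.04–1.14
- 14 days: 1.14–1.23
- 30 days: 1.33–1.58
- to the previous visit: 1.49 to about 2.2

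**4. More days at risk.** Now let every patient have the same act rate per suicidal day, with no effect of acts on the score; median remission 15, 30 or 60 days; 10% or 20% with an act. If acts occur only before the first zero, the odds ratio is 4.9–6.2. If the rate merely halves after it, the odds ratio is 1.2–1.6, with rejection in 6–23% of trials. Here acts and suicidality are related. What is absent is any higher daily risk in slow remitters.

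**5. Landmark check.** In every scenario of step 3, fixing remission status at day 91 and counting only later acts returned the odds ratio to 0.98–1.02 and the rejection rate to 3.5–5.3%.

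**The case against.** The strongest reply is that the reverse route depends on facts the article does not give. An act delays the zero only if its item enters the score and the act falls in the look-back of an assessment that would otherwise be zero. Item 13 concerns self-injury without suicidal intent, so whether it counts is especially unclear. An early act can also be followed by a zero before the median. This stands. A reader might infer that any act before the first zero makes the patient slow, or that an odds ratio near 2 is to be expected. The documents support neither. With a short look-back and day-level dating the reverse route all but disappears, so finer dating does help.

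Nor do the ratios of 4.9–6.2 show what happens when acts and remission are unrelated, because in that scenario acts occur only while the patient is suicidal.

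It is also fair that this is one of 14 listed factors in a second exploratory aim, worded as an association, with results labelled hypothesis-generating. That lowers the weight of the point. But the label is attached to the absence of multiplicity adjustment and does not address time order, while the aim itself speaks of risk factors. Including the T1–T2 interval as a covariate does not establish whether remission or the act came first.

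Finally, a fuller plan may handle time order. The article, however, states both windows explicitly and they overlap. A fuller plan would have to change that rule, not just add detail to it.

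**Conclusion.** The point holds as a problem of time order. As written, the analysis relates a classification made during follow-up to events counted over the same follow-up, on the same scale. It can therefore yield an association without slow remission preceding or predicting acts. Under strict independence the odds ratio lies between about 1.0 and about 2.2, depending on the scored items, the look-back and how the zero is dated, all of which are assumed here. Unequal time at risk adds a second route that needs no scoring assumption, and item 3 is close to circular.

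A reader might conclude that the study's data cannot show which came first. That goes too far: the landmark analysis uses the same data and can show it. Given the exploratory status, this is a correction worth making because it is cheap. It does not undermine the study's main aims.

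**What to change.** Set a landmark at a fixed time after T1, for example the month-3 assessment (T3), at which Table 1 schedules the S-STS. Classify remission as known at that point. Count items 12, 13 and 14, and new or returning item 3, only afterwards. Where Table 1 drops T3 because discharge falls within two weeks of it, say which S-STS value stands in. Where dates of remission and acts are available, entering remission as a time-dependent covariate is an alternative. State the scored items and the look-back. Report acts before the landmark, including those during inpatient treatment, descriptively.

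T2 is a poor landmark. Trial design allows discharge to come after T3 or coincide with T4, which leaves some patients little or no later follow-up, and the statistical section itself says discharge timing depends on the outcome. A simulated T2 landmark with person-time gave a rate ratio of 0.99–1.01, but the described inputs are a lognormal stay with no stated link to the outcome, so the result cannot be relied on here.

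The cost is precision: acts before the landmark, and patients lost before it, leave the predictor analysis. No new data are needed for a landmark placed at T3, provided the later interviews cover the time since then. The time-dependent version needs dated acts, which the article does not confirm.

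### Exploratory aim 2 defines slower resolution as a shorter-than-median time to S-STS zero, and its factor list omits two of the 14 hypothesised factors, quality of life and baseline suicidality

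*Protocol article*

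**What the plan says.** All places are in the protocol article.

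**Direction.** Under Aims and hypotheses, exploratory hypothesis 2 links active suicidality to "i) slower rate of remission of suicidal symptoms after baseline, greater baseline severity of (ii) depressive symptoms" and further factors. Under Sample size and statistical analyses, the paragraph on exploratory objectives restates the first factor as "slower initial resolution of suicidality (lower than median time to S-STS score = 0". Earlier in that section the median split is introduced with two groups "which are either below or above the median time to first complete remission of suicidality", neither of them named slow or fast. A later sentence plans "comparisons between the slower and faster remitting group of continuous variables" without saying which side of the median is which.

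**Factor list.** Exploratory hypothesis 2 includes "vi) quality of life impairment (vii) global illness symptoms, and (viii) suicidality" among its baseline severity factors. The matching list in the statistical section runs from the symptom scales through "anger/hostility (STAXI, AF-BP), and global illness symptoms (CGI-S); higher number of lifetime depressive episodes" and ends with "non-adherence to pharmacological and non-pharmacological treatments; comorbid borderline personality; and substance abuse diagnoses". It names neither quality of life nor baseline suicidality. The regression variables given after hypotheses 3A to 3D do include both: "quality of life (EQ-5-DL), and suicidality (S-STS); presence of psychiatric emergencies".

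**The concern.** The parenthetical is the only place in the article that assigns a side of the median to the slower group, and it assigns the wrong one. An analyst who programs it as written labels the faster resolvers as slow. The outcomes are active ideation, preparatory action, self-injury without suicidal intent and suicide attempt, so a reversed sign would point to the wrong risk group. No significance test would reveal it, because the p-value does not change.

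The omission is a separate matter. Two factors are hypothesised but not listed for analysis. Baseline suicidality is the more important of the two. It could plausibly influence both the time to reach zero and later active suicidality, and the protocol itself proposes it as a predictor of duration and recurrence in hypotheses 3C and 3D. If it is left out, an association with resolution speed may partly be an association with baseline severity.

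**Working it through.** **1. Figures in the plan.** No sample size or effect size is stated for exploratory aim 2. The nearest figure, PP3 enrolment, reproduces: 315 × (1 − 0.34) = 207.9, against the stated 208. The point does not depend on it.

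**2. Direction.** Let T be the time from T1 to the first S-STS score of zero, and m its median.
- T < m means zero was reached sooner, which is faster resolution.
- T > m means zero was reached later, or not by then, which is slower resolution.

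The label says slower and the parenthetical says T < m. Both cannot hold.

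**3. Effect of literal coding.** With z = 1 for T > m, let logit(p) = α + βz. Literal coding uses w = 1 − z, so logit(p) = (α + β) − βw. The slope changes sign and its standard error does not. The odds ratio becomes exp(−β) = 1/OR, the confidence limits become reciprocals and swap places, and the p-value is unchanged. For an assumed OR of 2.0, the result is 1/2.0 = 0.5.

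**4. Factor lists side by side.**

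| Factor in exploratory hypothesis 2 | In the exploratory analysis list? |
|---|---|
| (i) slower remission | yes, with the reversed definition |
| (ii) depressive symptoms | yes (MADRS, QIDS-S) |
| (iii) manic symptoms | yes (YMRS) |
| (iv) anxiety | yes (BAI) |
| (v) anger and hostility | yes (STAXI, AF-BP) |
| (vi) quality of life | **no** |
| (vii) global illness | yes (CGI-S) |
| (viii) baseline suicidality | **no** |
| (ix) lifetime episodes | yes |
| (x) duration of current episode | yes |
| (xi) psychiatric emergency | yes, worded as frequency |
| (xii) non-adherence | yes |
| (xiii) borderline personality | yes |
| (xiv) substance use diagnosis | yes |

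That is 14 − 2 = 12 carried over. Table 1 shows that both missing variables are collected at T1: the S-STS in the PP2 block and the EQ-5-DL in the PP3 block.

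**5. What the omission could do.** The documents give no correlations or effect sizes, so every input here is an assumption. In a simulation of 200,000 patients, the true OR for slow (T > m) was set at 2.0 and the intercept at −1.5. Quality of life had a log-OR of 0.2 per SD and a correlation of 0.3 with baseline suicidality. The correlation of baseline suicidality with time to zero, and its log-OR per SD, were varied. The table gives the OR for slow when both variables are left out and nothing else is adjusted for.

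| Correlation with time to zero | log-OR 0 | log-OR 0.4 | log-OR 0.8 |
|---|---|---|---|
| 0 | 2.01 | 1.95 | 1.86 |
| 0.3 | 2.08 | 2.41 | 2.60 |
| 0.5 | 2.10 | 2.75 | 3.38 |

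With both variables in the model, the OR was 1.95 to 2.04 throughout, and 0.49 to 0.51 under the literal coding. The values below 2 in the zero-correlation row reflect the non-collapsibility of the odds ratio, not confounding.

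A second simulation assumed no true effect of resolution speed, a correlation of 0.3 to 0.5, and a baseline OR of 1.5 to 2.0 per SD. It gave unadjusted ORs of 1.20 to 1.69, and 0.99 to 1.02 after adding the baseline score.

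Both simulations compare no adjustment with full adjustment. The listed analysis includes MADRS, QIDS-S, CGI-S, BAI and other factors, which may carry part of baseline severity. The figures therefore show the mechanism; they do not estimate the bias in the planned analysis.

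**The case against.** The strongest reply is that this is a slip of wording in a condensed article. The word slower, exploratory hypothesis 2 and the slower and faster remitting groups all show the intended direction. A flipped binary code loses no information and can be put right by relabelling. The sentence with the factor list reads as a restatement of the hypothesis and names no model or adjustment set. Multivariable regression with backward selection is planned in the same section without a stated candidate set, and both missing variables appear in the regression list after hypotheses 3A to 3D. The full protocol or analysis plan, which is not shown, may settle the covariates.

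Much of this stands. A reader might infer that the reported effect will be inverted and confounded. The documents do not support that. Inversion follows only if the parenthetical is programmed literally, against its own label. Confounding follows only if the list is the candidate set and the listed severity scales fail to carry baseline suicidality. The stated aim is to find risk factors, not to estimate a causal effect of resolution speed. Nor do the documents show that a primary result is at risk: the article says that p-values and intervals are to be read as hypothesis-generating.

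Two things remain. The only operational rule for the slower group is a wrong statement, not a detail left to another document. The factor list departs from the hypothesis it serves, while spelling out the other twelve factors, several with their instruments. The exploratory label excuses the lack of multiplicity adjustment but explains neither discrepancy.

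**Conclusion.** The point holds as two textual errors with conditional consequences. The definition of slower resolution is reversed. Followed literally, it yields the reciprocal odds ratio (0.5 for an assumed 2.0) with an unchanged p-value. The analysis list omits two of the 14 factors in exploratory hypothesis 2. As listed, these would go untested, and the association with resolution speed could partly reflect baseline suicidality. How large that part is cannot be said from the documents. Under the assumptions shown, and with no other covariate, it ranges from almost nothing to an OR of about 3.4 in place of 2.0, and the listed severity scales may reduce it. Severity is minor to moderate: the aim is exploratory, and no primary objective, sample size or primary model is touched.

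**What to change.** **Definition.** Replace the parenthetical with: longer than the median time to S-STS score = 0. Count a patient not observed to reach zero as slow only if followed beyond the median. A patient lost before the median without reaching zero cannot be classified, and the text should say how such patients are handled. At the planned attrition, up to 315 − 208 = 107 patients will lack month-6 data. Some of them will have reached zero or passed the median before leaving.

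**Factor list.** Add the T1 S-STS score and the EQ-5-DL, to match exploratory hypothesis 2 and the regression variables listed after hypotheses 3A to 3D.

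**Cost.** The first change is a wording correction. The second needs no new data but has a small downside. Two more candidate predictors take 2 × 10 = 20 patients under the protocol's own rule of 10 per predictor. They weigh more for rarer outcomes such as suicide attempts, for which no event numbers are given. The baseline S-STS score also overlaps with outcomes defined by S-STS items, and a score of at least 1 on item 2 or 3 is a PP3 entry criterion. The overlap should be acknowledged when the results are read.
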